#### Pre-Analysis

##### Power Analyses

The sample size for analyses for data relating to the primary objective has been calculated for a repeated measures analysis of variance: based on an alpha of .05, a minimal detectable effect size of f2=.15, and a power of .80, a total number of 55 participants [80] is required in each group to answer the primary research question of this study in a statistically valid manner.

We expect to be able to include 330 eligible participants within a period of 2 years, based on a mean of 3.7 intakes per week for the eMBCT of the Helen Dowling Institute in 2011. An estimated attrition of 30% of the participants during both experimental interventions and 15% during the minimal intervention control condition [51] would leave us with 77 participants in each experimental group and 94 participants in the control group at T2. Again, we expect a dropout rate of 30% during the second semester. Such a dropout would leave a total of 110 participants completing each experimental intervention. Ten percent of the participants may have to be excluded from the analyses because of recurrence or diagnosis of metastasis. That would result in 198 participants that complete the full trial. We expect that this number will be enough for testing the 6 mediating factors or effect predictors: A classical, conservative power calculation (analysis of variance for testing 6 mediators or effect predictors with an intermediate effect size (f2=.08), corrected according to Bonferroni (alpha=.05/6), and at a power of .80 [81]) would result in approximately 254 participants being needed. We expect that the actual power when including 198 participants, and not the required 254 participants, will be great enough to detect up to 6 mediators or effect predictors with the use of Bayesian statistics [76]. Bayesian statistics allow analysis on small sample sizes [76,77], as more power can be generated with the use of prior information which is incorporated in the model that is being tested. Various papers describe comparisons between traditional null hypothesis testing and Bayesian estimation [82-85]. For this study, prior knowledge is available for many parameters, such as the effects of mindfulness in cancer survivors [23,25,66,86] and the role of working alliance in online interventions [87]. Examples of these methods can be found in both applied psychology and social science articles [88-92].

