The fit of the piecewise model will be compared with a quadratic model. In the quadratic model, the entire first semester is modeled with 1 slope factor and 1 quadratic factor for each of the 3 conditions and an intercept that represents T0b and is constrained similarly to the piecewise model.

Both models will be run both with and without using time-varying loadings in order to check whether corrections should be made for differences in timings between the questionnaires. Growth factor estimates and model fits for all 4 models will be reported (Table 5).

Neither the participants nor the researchers ([name] and MW) are blinded to allocation. Therefore, an independent statistician ([name]) who is blind to the allocation will test the primary hypothesis.

The same procedure will be followed for the secondary outcomes, except that the initial intercept of mental health will represent T0a, rather than T0b, because T0b does not include an assessment of mental health.

Results of frequentist analyses will be reported by *P*-values (significant in case <.05) and with 95% confidence intervals. Parameter estimates of models by means of Bayesian estimators will be reported with 95% central credibility intervals.

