##### Mediators

###### Overview

The analysis of the mediators of the experimental conditions can be roughly subdivided into two steps: first analyze the primary factors individually for their longitudinal correlations with the outcome (Step 6), then combine the relevant factors in a multivariate analysis (Step 7). The specific hypothesis on the mediating factors of the interventions in this study are shown in Textbox 2.

###### Step 6

For analyzing the mediators of the experimental conditions, first we want to see whether there is a correlation between the growth trajectories of our outcome parameter and the potential mediator over time. The hypotheses considering mediators are shown in Textbox 2. The combined data from the participants in the first semester and data from the preferentially assigned participants in the second semester will be used.

The following subhypotheses will be tested for each primary mediator (these are also shown in Figure 5):

Is the growth of the primary outcome (Sy) for the entire study population correlated with growth of the potential mediator (Sz)?Is such correlation independent of group?Does the potential mediator change over time in the specific group, so is the slope factor (Sz) substantially unequal to zero?Is the slope factor in the specific group substantially greater than the slope factors in the other groups?

In these 4 subhypotheses, the first is congruent with testing the “conceptual theory” in classical mediation analysis, and subhypothesis 3 with testing the “action theory.” If subhypotheses 1-4 all are true, the factor will be considered a specific mediator for that intervention. If subhypotheses 1, 2, and 3—but not 4—are true, the factor will be considered a general mediator for fatigue severity. If either subhypothesis 1 (conceptual theory) or 3 (action theory) is false, the factor will not be considered a mediator.

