Hypotheses on mediators.We expect that, for AAF, increasing mean cumulative daily physical activity and reductions of daily physical activity decline are specific mediators.We expect that, for eMBCT, developing mindfulness skills is a specific mediator.We expect that sleep quality, working alliance, sense of control over fatigue, credibility, and expectancy are generic mediators for both e-therapies.The mediating role of the following factors will be explored: number of sessions completed, changes in causal attributions [99], decreased catastrophizing thoughts about fatigue [8], decreased fear of cancer recurrence [100,101], changes in perceived activity [102], increased self-efficacy on physical activity [103].

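### Step 6 calls a factor a general mediator when a larger slope is not shown, without requiring that the factor changed in the other intervention

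*Protocol article*

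**What the plan says.** In the protocol article (Analysis Plan, Mediators, Step 6), four subhypotheses are tested for each primary mediator. The first is that the growth of fatigue and the growth of the factor are correlated. The second asks "Is such correlation independent of group". The third asks "Does the potential mediator change over time in the specific group, so is the slope factor (Sz) substantially unequal to zero". The fourth asks "Is the slope factor in the specific group substantially greater than the slope factors in the other groups".

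If all four hold, the factor is labelled specific to that intervention. For the other label the rule is "If subhypotheses 1, 2, and 3—but not 4—are true, the factor will be considered a general mediator for fatigue severity". If the first or third is false, the factor is not a mediator. There is no undetermined category, no margin for similarity, and no threshold for a substantial difference. The only decision level in the analysis plan, under Effectiveness, Step 1, is "significant in case <.05", or a 95% credibility interval for Bayesian models.

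Textbox 2 makes generality a trial hypothesis: "We expect that sleep quality, working alliance, sense of control over fatigue, credibility, and expectancy are generic mediators for both e-therapies".

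**The concern.** Subhypotheses 1 to 3 give positive evidence that the factor moves with fatigue and that it changed in one intervention. Nothing in the rule gives positive evidence about the other intervention. The step from mediator to general mediator rests wholly on subhypothesis 4 not being met, and it can fail for lack of power as well as for lack of a difference.

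The two tests are unequal. Subhypothesis 3 compares one slope with zero. Subhypothesis 4 needs that slope to exceed the slopes of the other groups, so it carries the noise of two groups in each contrast and requires both contrasts. A truly specific factor can easily pass the third and fail the fourth, and it then counts in favour of the generic hypothesis in Textbox 2.

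What is at stake is a stated advantage of the three-arm design. The Introduction (Mediators) and the Discussion (Principal Findings) both say that it can separate treatment-specific from nonspecific mechanisms, and the Discussion wants such knowledge used in allocating patients.

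**Working it through.** **The plan's own mediator figure.** Power Analyses asks for about 254 participants with six factors, f2 = .08, "corrected according to Bonferroni (alpha=.05/6), and at a power of .80". An overall F test with 6 numerator degrees of freedom and noncentrality 0.08 × N gives N = 252, which agrees. At the 198 participants the plan expects, power is 0.64. This calculation does not address subhypothesis 4.

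**Group sizes, from Power Analyses.** Each arm starts with 330/3 = 110. First semester: 110 × 0.70 = 77 per intervention and 110 × 0.85 = 93.5, about 94, in control. Step 6 pools both semesters: 77 + (94 × 0.70)/2 ≈ 110 per intervention. Neither set is reduced for the 10% recurrence loss, so both are slightly favourable to the plan.

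**Assumptions.** The mediator slope is d SD in one intervention and 0 in the other two groups. Slopes are normal and independent, tests are two-sided at .05 (the article does not state sidedness), and subhypotheses 1 and 2 are taken as met. The values of d are mine; the article gives none.

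**Worked case, d = 0.4, 77/77/94.**
- Subhypothesis 3: z = 0.4 × √77 = 3.51; power Φ(3.51 − 1.96) = 94%.
- Contrast with the other intervention: standard error √(1/77 + 1/77) = 0.161; z = 2.48; power Φ(0.52) = 70%.
- Contrast with control: standard error √(1/77 + 1/94) = 0.154; z = 2.60; power Φ(0.64) = 74%.
- Both contrasts met (simulated, since they share an arm): 58%.
- Subhypothesis 3 met and 4 not met, so labelled general: 36%.

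**All cases (simulation).**

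| Groups | d (SD) | Subhyp. 3 met | Subhyp. 4 met | Labelled general | Of these, other intervention not significant |
|---|---|---|---|---|---|
| 77/77/94 | 0.3 | 75% | 32% | 44% | 94% |
| 77/77/94 | 0.4 | 94% | 58% | 36% | 92% |
| 77/77/94 | 0.5 | 99% | 81% | 18% | 88% |
| 110/110/94 | 0.3 | 88% | 42% | 46% | 94% |
| 110/110/94 | 0.4 | 99% | 72% | 26% | 91% |
| 110/110/94 | 0.5 | 100% | 92% | 8% | 85% |

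The label rate is not exactly the third column minus the fourth, because subhypothesis 4 is occasionally met when 3 is not. The 110/110/94 rows are approximate: former control participants contribute twice, so the pooled records are not independent.

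**At the plan's own effect size.** In two-group terms f2 = .08 corresponds to d = 2 × √0.08 = 0.57. The false label is then 8.5% at 77/77/94 and 3% at 110/110/94. At 0.8 SD it is 0.2% or less.

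**Sensitivity to alpha.** If the .05/6 of the power calculation were also used in Step 6, the rates for 0.3, 0.4 and 0.5 SD would be 39%, 51% and 40% at 77/77/94, and 52%, 50% and 26% at 110/110/94.

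**The case against.** **The label is only a working classification.** The article says a factor will be considered general, not that slopes are equal or that generality is proven. That stands, and a reader who infers that the plan would declare generic mediation confirmed goes further than the text. The label still answers a Textbox 2 hypothesis, so it needs evidence behind it.

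**Step 7 comes afterwards.** It fits one model per intervention against control and removes factors with an insignificant indirect effect, so a mislabelled factor can drop out of the other intervention's model. But Step 7 does not compare the interventions or revise the Step 6 label.

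**The rule could be run with each intervention in turn as the specific group.** A factor that moved only in one would then be general in one run and not a mediator in the other. Step 6 does not say how such conflicting results are reconciled. If the sponsor means that change is needed in both, writing it down is most of the fix.

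**Bayesian estimation may supply power.** Prior information can narrow intervals, but an interval that includes zero is still no evidence of similarity.

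Three stronger readings are tempting and not supported:
- *A smaller sample makes the general label easier to obtain.* It does not, because subhypotheses 1 and 3 also need power. For a truly specific factor at 0.3 SD, the false label rises from 21% at 20 per arm to 46% at 110/110/94.
- *A missed group difference in the correlation turns a specific factor into a general one.* Subhypothesis 2 is required for both labels, so only subhypothesis 4 separates them.
- *The chance of missing subhypothesis 4 is the error rate.* Subhypothesis 3 must also be met. At 40 per arm and 0.5 SD, subhypothesis 4 is missed in about 56% of runs, but the label is given in 44%.

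**Conclusion.** The point holds. As written, Step 6 treats failure to show a larger slope as generality and asks for no change in the other intervention. For assumed slopes of 0.3 to 0.5 SD in one arm only, the false general label occurs in roughly 18 to 44% of runs at the first-semester sizes and 8 to 46% at the planned pooled sizes. Mostly the other intervention shows no significant change.

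The size depends on the assumed slopes, on alpha .05, on independent records and on subhypotheses 1 and 2 being met. At the planned sizes the problem is small above about 0.6 SD. It concerns the second objective, not the primary comparison on fatigue. It is worth correcting because the rule is stated explicitly, errs towards a trial hypothesis, and can be repaired without new data.

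**What to change.** Reword the Step 6 rule:

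1. Give the label general only if the mediator slope Sz is non-zero in the expected direction in both AAF and eMBCT.
2. Report the AAF-minus-eMBCT difference in Sz with its interval in every case, and claim similarity only if that interval lies within a margin stated beforehand.
3. If subhypotheses 1 to 3 hold but neither label is earned, report the factor as a mediator with specificity not determined.

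In the cases above, the first condition alone lowers the false general label to about 1 to 3%. A margin alone is not enough: adding only ±0.5 SD to the present rule at 110/110/94 leaves 31% and 15% false labels at 0.3 and 0.4 SD.

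No new data are needed, since both interventions are already assessed. The cost is that some truly generic factors with small slopes become undetermined. With 0.3 SD in both interventions and none in control, the general label falls from 73% to 56% at 77/77/94 and from 86% to 77% at 110/110/94. A similarity claim also needs a realistic margin. With no true difference, 80% power and a 90% interval, n per arm = 2 × ((1.645 + 1.282)/margin)², which gives 69 for ±0.5 SD, 108 for ±0.4, 191 for ±0.3 and 429 for ±0.2. These margins are illustrations; the sponsor should choose one and justify it.

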##### Effect Predictors

###### Overview

Two complementing approaches for analyzing the effect predictors are addressed in steps 8 and 9 of this analysis plan. The specific hypotheses on the effect predictors for both interventions in this particular study are shown in Textbox 3. 

Hypotheses on effect predictors.We expect that for AAF, low perceived physical activity predicts reduction of fatigue severity.We expect that for eMBCT, low perceived concentration, previous experience with mediation exercises, high perceived life threat from cancer, and a high education level predict reduction of fatigue severity.In general, we expect that low perceived social support, longer time since last treatment, suffering from more comorbidities [108], and having strong somatic attributions [57] predict small effects on fatigue severity in both interventions. We expect that high sense of control and good sleep quality predict large effects in both experimental conditions.Other factors will be included for explorative research.

###### Step 8

To find out which participants benefit most from each intervention, the final model of fatigue severity of Step 1 will be extended with potential effect predictors (Textbox 3) that load on the latent growth factors “linear slope” (the “post randomization” linear slope in case of the piecewise model) and, if applicable, “quadratic slope.” As the regression coefficients of all potential effect predictors on the development of fatigue severity will be freely estimated across the 3 intervention groups, this is also called a moderation effect of intervention.

Factor loadings of all hypothesized effect predictors will be reported. Those with the highest loadings will be compared between the conditions in order to find differential effect predictors.

###### Step 9

To identify common effect predictors of homogeneous subpopulations within the heterogeneous population, rather than identifying effect predictors for individual growth patterns, the final step will consist of regressing predictors on latent classes. Therefore, the final model of Step 5, the GMM, will be extended. Again, several potential effect predictors will be regressed onto this model, but this time on the latent class factor, instead of on the latent growth factors. The 3-step procedure proposed by Vermunt [109] will be used for model selection. This step will be carried out separately for each experimental condition.

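### Step 6 awards the 'general mediator' label without a contrast with control, and Steps 8 and 9 do not require the contrast that separates effect predictors from prognostic factors

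*Protocol article*

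**What the plan says.** **Step 6** (Analysis Plan, Mediators) sets four subhypotheses for each primary mediator:
1. its growth correlates with growth of fatigue;
2. that correlation does not depend on group;
3. "Does the potential mediator change over time in the specific group, so is the slope factor (Sz) substantially unequal to zero";
4. its slope in that group exceeds the slopes in the other groups.

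The plan equates subhypothesis 3 with testing action theory. All four true gives a specific mediator for that intervention. If 1, 2 and 3 hold but 4 does not, "the factor will be considered a general mediator for fatigue severity". Textbox 2 expects sleep quality, working alliance, sense of control, credibility and expectancy to be generic mediators of both e-therapies.

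**Step 7** fits a multiple-mediation model for each intervention, with X coded as that intervention versus control. It removes factors whose indirect effect a × b is not significant. Its starting model takes only the significant primary mediators of Step 6 that were also assessed in the control group.

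**Step 8** (Effect Predictors) estimates predictor coefficients freely in the three groups and calls this a moderation effect. It reports the loadings of all hypothesized predictors, then: "Those with the highest loadings will be compared between the conditions in order to find differential effect predictors".

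**Step 9** regresses predictors on the latent classes of Step 5, which are formed within the experimental groups: "This step will be carried out separately for each experimental condition". It closes with the same comparison of the highest loadings.

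**The concern.** Action theory is the path from treatment to mediator. Step 7 defines that path as intervention versus control, whereas Step 6 tests it as change over time inside one arm. These are different quantities.

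Failing subhypothesis 4 covers two different situations. In one, both therapies move the factor and control does not, which is what Textbox 2 appears to mean by generic. In the other, the factor drifts equally in all three arms. The second cannot account for any difference from control, yet the rule gives both the same name.

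Steps 8 and 9 have a related weakness. A factor that predicts the course of fatigue equally in every arm is prognostic. An effect predictor is one whose coefficient differs between arms. Free estimation allows a difference but does not show one. Ranking on loading size favours factors that are strongly prognostic everywhere and can pass over a true moderator with modest loadings. Step 9 has no control arm to compare with.

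The stakes are objectives 2 and 3 of the trial. The Discussion says that knowledge of differentiating factors should be used to allocate patients to suitable interventions.

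**Working it through.** **The plan's own figure.** Power Analyses gives a calculation for six mediators or predictors "with an intermediate effect size (f2=.08"), "corrected according to Bonferroni (alpha=.05/6), and at a power of .80", which "would result in approximately 254 participants being needed". Taking the noncentral F test with 6 numerator df, λ = f²·N and α = 0.05/6 = 0.00833, power first reaches 0.80 at N = 252. The stated 254 is reproduced to within 1%. At the 198 completers the plan expects, the same classical test has power 0.64. This figure does not test the labelling rules, so those were checked separately.

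**Step 6: inputs**
- Arm sizes: "77 participants in each experimental group and 94 participants in the control group at T2", so 77/77/94 and N = 248.
- Every 'substantially' is read as P < .05, the plan's level for frequentist tests (assumption).
- The mediator has the same trend in all three arms: 0, 0.2, 0.3 or 0.5 SD of the individual slopes (assumption; the document gives none).
- The mediator slope correlates with the fatigue slope at 0.2, 0.3 or 0.5, equally in all arms (assumption).

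Treatment therefore has no effect on the mediator. The rates below are for one given experimental arm, from 20,000 simulated trials per setting.

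| Common trend | Labelled 'general mediator' | Same, if a difference from control is also required | Labelled 'specific mediator' |
|---|---|---|---|
| 0 | 4–5% | 1.3–1.5% | 0.3–0.4% |
| 0.2 SD | 34–39% | 1.8–1.9% | 0.4–0.5% |
| 0.3 SD | 62–70% | 1.8–2.1% | 0.3–0.5% |
| 0.5 SD | 83–94% | 3.5–4.0% | 0.4–0.5% |

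**Hand check at correlation 0.2**
- Subhypothesis 1: arctanh(0.2)·√(248 − 3) = 0.2027 × 15.65 = 3.17, so power is Φ(3.17 − 1.96) ≈ 0.89.
- Subhypothesis 2 is true and is retained in about 95% of trials.
- Subhypothesis 3: a one-sample t test at n = 77 has power 0.41, 0.74 and 0.99 for trends of 0.2, 0.3 and 0.5 SD.
- Products: 0.89 × 0.95 × 0.41 ≈ 0.35; × 0.74 ≈ 0.63; × 0.99 ≈ 0.84. The simulation gives 0.34, 0.62 and 0.83.

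The label rate is thus essentially the power to detect a time trend in one arm.

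**Step 8.** Take a purely prognostic factor with the same standardized coefficient in all arms (values assumed). The plan ranks loadings without naming a test, so significance within an arm serves here as a proxy for being singled out.

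| Coefficient in every arm | Significant in a given experimental arm | In at least one of the two | Difference from control significant |
|---|---|---|---|
| 0.2 | 42% | 66% | 5% |
| 0.3 | 77% | 94% | 5% |
| 0.4 | 96% | 99.8% | 5% |

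With coefficients of 0.2 or 0.3, the factor is significant in exactly one of the two experimental arms in 49% or 36% of trials, although the true coefficients are equal. Side-by-side reading of within-arm results can therefore suggest a differential predictor where none exists.

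Textbox 3 names 11 predictors. If all were pure noise, the largest absolute loading in one arm of 77 would average about 1.92/√74 = 0.22, so there is always a highest loading to compare.

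**Limits.** The simulations use observed slope scores in place of the latent growth model. They also leave out the preference-allocated second-semester data that Step 6 pools.

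**The case against.** A reader might infer that Steps 6, 8 and 9 as a whole rest on within-arm change, so that time trends and prognosis would routinely be reported as mechanisms and moderators. The document does not support that.

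- **Specific mediators.** This label requires a slope greater than in the other groups. The hypotheses on activity for AAF and mindfulness for eMBCT are of this kind, and the false rate stays near 0.3% to 0.5%.
- **Step 7.** It tests a × b against control and would remove most common-trend factors from the final model. The 34% to 94% is the pass rate of the Step 6 label, not of the whole mediation analysis.
- **Step 8.** Control is one of its three groups, selected loadings are compared between conditions, and all hypothesized loadings are reported.
- **Shared mechanisms.** The Introduction wants nonspecific working mechanisms studied, and the control emails overlap fully with information given in both interventions. Equal change in all arms may be a real shared process. It cannot explain an effect versus control, but saying that it explains nothing would go too far.
- **Size of trend.** The Introduction says that fatigue lasting 3 months after treatment is unlikely to decrease by itself, so a large common trend is not assured.

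These points narrow the concern without removing it. Nothing withdraws the Step 6 label after Step 7, and Step 7 itself describes its inputs as factors already shown to be mediators. Primary factors without control data never enter its starting model. Working alliance is plausibly one of these, since controls have no therapist, and for it Step 6 would be the only verdict. In Step 8 the comparison follows selection on loading size, and free estimation is itself called moderation.

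**Conclusion.** The concern holds in a limited form. The 'general mediator' rule in Step 6 lacks a contrast with control and cannot tell a factor moved by both therapies only from one that changes equally in all arms. This follows from the rule and needs no simulation. Its size depends on assumed trends and correlations: about 34% to 94% false labels for common trends of 0.2 to 0.5 SD, 4% to 5% with none, and about 1% to 4% once a difference from control is required.

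The moderation wording and highest-loading screen in Step 8, and the absence of control from Step 9, leave prognostic factors and effect predictors insufficiently separated. The plan should be changed. The primary effectiveness analysis and the 'specific mediator' label are not affected.

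**What to change.** **Step 6.** Require a slope difference from control before calling a factor a mediator of an intervention effect. Use the AAF-versus-eMBCT slope difference to separate specific from generic. Report factors that change equally in all arms as correlates of fatigue change, possibly reflecting shared nonspecific processes. Keep factors not measured in control descriptive.

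**Step 8.** Drop the highest-loading screen. For every Textbox 3 predictor, report the coefficient difference with its confidence interval for each experimental arm versus control and for AAF versus eMBCT. The last contrast is the one that bears on choosing between the two therapies.

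**Step 9.** Describe predictors as within-arm (prognostic) unless the Step 8 contrasts support a differential effect.

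**Cost.** The changes are to wording, plus contrasts in the same models; no new data are needed. Contrasts are less precise than within-arm estimates. With arms of about 69 and 84 (77 and 94 less the plan's 10% exclusion, an assumption), the standardized SE is √(1/66 + 1/81) = 0.17 against √(1/66) = 0.12. At 77 and 94 it is √(1/74 + 1/91) = 0.16 against √(1/74) = 0.12. Some factors will be left undecided.
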